### Periodontal clinical examination

The periodontal clinical examinations will be conducted by one single calibrated examiner to assess the periodontal status of each participant. Clinical examinations will be performed using a 10-mm round-tip manual Williams periodontal probe. All permanent teeth, excluding the third molars, will be examined at six sites per tooth (disto-buccal, mid-buccal, mesio-buccal, disto-palatal, mid-palatal, mesio-palatal). Visible plaque (VP), gingival recession (GR), periodontal probing depth (PD) and bleeding on probing (BOP) will be recorded. Clinical attachment loss will be obtained by the sum of GR and PD.

### Subgingival biofilm

The supragingival biofilm will be removed using sterile cotton and curettes. Relative isolation will be conducted in the area to be sampled. The subgingival biofilm samples will be obtained using no. 30 sterile paper points inserted for 1 min in the pocket. Paper points will be stored in one Eppendorf tube at −20°C until analyzed. The four deepest sites of each individual will be sampled.

The presence of periodontopathogenic bacteria in the subgingival biofilm will be assessed by real-time polymerase chain reaction (RT-PCR). Three species will be evaluated (*T. forsythia*, *P. gingivalis* and *T. denticola*).

### Endothelial function

Non-invasive measurements of endothelial function will be conducted by flow-mediated dilation (FMD) of the brachial artery using bidimensional ultrasound equipment. Individuals will have to be rested and will lay in a controlled-temperature room. All vasodilation medication will have to be interrupted for at least 4 h before the examination, if possible. Individuals will also be advised to refrain from exercising, drinking caffeine and smoking for at least 4 h before the examination. The examination will start after 15 min of rest in the supine position with the arms in a comfortable position. An image of the brachial artery will be obtained above the antecubital fossa in a longitudinal plane. The flow will be monitored with the Doppler positioned at a 65^o^ angle, and images will be obtained between the lumen and the wall of the vein. A sphygmomanometer will be inflated at the right forearm for 5 min, at least 50 mmHg above the systolic pressure, for measurement of reactive hyperemia. Images will be established 30 s before and until 2 min after sphygmomanometer deflation, synchronized with the “R” wave of the electrocardiogram. FMD will be expresses as the relative variation of the brachial diameter in the hyperemic phase and defined as [(post-hyperemic diameter – baseline diameter)/baseline diameter] × 100.

After 15 min of the reactive hyperemic measurement and artery diameter normalization, the baseline artery diameter will be measured again. In the sequence, a dose (spray) of sublingual NTG will be administered to evaluate dependent endothelial vasodilation with images acquired after 5 min [26].

### Demographics, behavioral and clinical variables

A structured questionnaire will be applied to all participants to obtain demographic and behavioral data. Age, socioeconomic level, education, medication use, smoking habits and frequency of physical activities will be recorded. Individuals will be examined clinically to measure height, weight and blood pressure. Body mass index (BMI) will be calculated dividing the weight by the square of the height.

### Primary outcome

The primary outcome of the present trial will be changes in serum concentrations of C-reactive protein.

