**Methods/design:**

This is a randomized, parallel design, examiner blinded, controlled clinical trial. Individuals from both genders, 35 years of age and older, with concomitant diagnosis of CAD and periodontitis will be included. CAD will be defined as the occurrence of at least one of the following events 6 months prior to entering the trial: documented history of myocardial infarction; surgical or percutaneous myocardial revascularization and lesion >50% in at least one coronary artery assessed by angiography; presence of angina and positive noninvasive testing of ischemia. Diagnosis of periodontitis will be defined using the CDC-AAP case definition (≥2 interproximal sites with clinical attachment loss ≥6 mm and ≥1 interproximal site with probing depth ≥5 mm). Individuals will have to present at least ten teeth present to be included. One hundred individuals will be allocated to test (intensive periodontal treatment comprised by scaling and root planing) or control (community periodontal treatment consisting of one session of supragingival plaque removal only) treatment groups. Full-mouth six sites per tooth periodontal examinations and subgingival biofilm samples will be conducted at baseline, 3, 6 and 12 months after treatment. The primary outcome of this study will be C-reactive protein changes over time. Secondary outcomes include levels of total cholesterol, LDL-C, HDL-C, triglycerides, IL-1β, IL-6, TNFα, fibrinogen, ICAM-1, VCAM-1 and E-selectin. These outcomes will be assessed at all time points over 12 months. Flow-mediated dilation will be assessed at baseline, 1, 3 and 6 months after periodontal therapy.

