### Sample size

The sample size of the present trial was estimated using a statistical software (G*Power 3 for Macintosh). The change in serum levels of C-reactive protein was considered the main outcome for sample size estimation. It was estimated that 42 individuals in each treatment arm will be necessary to find reductions in C-reactive protein of 1.5 mg/l (standard deviation = 1.5) and 0.5 mg/l (standard deviation = 0.5) in the test and control groups, respectively. Alpha and beta errors of 5% and 20%, respectively, were used in the estimation. An attrition rate of 20% is expected during the study; consequently, 50 patients in each group will be included.

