### Blood markers

Each individual will provide two 10-ml samples of blood collected by a trained nurse from the antecubital fossa. Fasting blood samples will be obtained between 7:00 a.m. and 12:00 p.m. to control for possible diurnal variations. Blood samples for traditional cardiovascular blood markers will be immediately centrifuged and analyzed. Blood samples used for proinflammatory and endothelial markers will be centrifuged at 4°C and 4.000 rpm for 10 min (ALC PK 120 R, ALC International, Milan, Italy). The serum will be sampled and stored in Eppendorf tubes at −80°C until analysis.

Traditional cardiovascular blood risk markers to be assessed will be glucose, glycated hemoglobin, triglycerides (TG), total cholesterol, and high- and low-density lipoprotein cholesterol (HDL-C and LDL-C). The following proinflammatory markers will be assessed: C-reactive protein, interleukin 1β (IL-1β), IL-6, tumor necrosis factor α (TNFα) and fibrinogen. ICAM-1, VCAM-1 and E-selectin will be the measured to assess the endothelial function. These markers will be measured at baseline, 3, 6 and 12 months after treatment.

High-sensitive CRP, glucose, TG, total cholesterol and HDL-C will be measured by automated enzymatic colorimetric methods (ADVIA 1800, Siemens, Germany) following the manufacturer’s instructions. CRP will be measured using the intensified immunoturbidimetry by latex (CRP_2). Glucose will be obtained using the glucose-hexokinase method II (GLUH). Total cholesterol will be dosed by the colorimetric enzymatic method (CHOL_2) with cholesterol-esterase and cholesterol oxidase followed by a Trinder type endpoint. Triglycerides will be measured by the Trinder GPO method. HDL-C will be assessed by the HDL-*Directo* (HDL-D) using the principles of elimination/catalase. LDL-C will be calculated using the Friedwald formula [LDL-C = total cholesterol – (HDL-C + TG/5)]. Non-HDL-C will be calculated by the subtraction of HDL-C from total cholesterol. Very low density lipoprotein cholesterol (VLDL-C) will be calculated dividing TG by 5. Glycated hemoglobin will be obtained by high-precision chromatography (Merck-Hitachi L-9100, Merck, Germany).

Proinflammatory and endothelial function blood markers will be measured using specific kits for Luminex (Milliplex map human panels, EMD Millipore Corp., Billerica, MA, USA).

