### Statistical analyses

Continuous variables will be described using means and standard deviations or median and range in case of asymmetric distribution of data. Categorical variables will be presented using frequency distribution. An intention-to-treat approach will be used in the analysis of this trial taking into consideration all dropouts during the follow-up period.

Univariate analyses will be conducted using chi-square and *t* tests for independent samples. Multivariate models will be fitted using generalized estimating equations to compare changes in each outcome according to test and control periodontal treatment groups controlling for confounding factors. *P* values <0.05 will be considered statistically significant. A statistical package (Stata 12 for Macintosh, STATA Corp., College Station, TX, USA) will be used. The individual will be considered the unit of analysis.

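### The primary outcome, change in CRP, is not tied to one contrast, so the test to which the 5% error rate applies is not fixed

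*Protocol article*

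**What the plan says.** The Primary outcome section reads: "The primary outcome of the present trial will be changes in serum concentrations of C-reactive protein". The abstract adds a time element but no time point: "The primary outcome of this study will be C-reactive protein changes over time". Under Blood markers, the schedule for CRP and the other markers is: "These markers will be measured at baseline, 3, 6 and 12 months after treatment". That gives three follow-up values per patient.

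The Sample size section works from one pair of means, "reductions in C-reactive protein of 1.5 mg/l (standard deviation = 1.5) and 0.5 mg/l (standard deviation = 0.5) in the test and control groups", and does not say at which visit they apply. It adds: "Alpha and beta errors of 5% and 20%, respectively, were used in the estimation".

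The Statistical analyses section lists chi-square and t "tests for independent samples" as univariate analyses. It then says: "Multivariate models will be fitted using generalized estimating equations to compare changes in each outcome according to test and control periodontal treatment groups", with control for confounders. The threshold is that P "values <0.05 will be considered statistically significant". No CRP result is ranked above another. The covariates listed under Independent/exposure variables and confounding do not include baseline CRP.

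**The concern.** The time point or summary measure is part of what a primary outcome is. Here, four or more contrasts fit the wording: a difference at 3, 6 or 12 months, an average of the three, or a joint test across them. They can disagree. Under Interventions, the test group is seen monthly for six months and then every three months, while the control group has a single session. The treatment difference may therefore change over follow-up, and the same data could be positive on one contrast and negative on another.

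Two things are at stake. First, the 5% alpha used for the sample size describes one test, and the article does not say which. Second, a reader of the results could not tell whether the reported contrast was chosen before or after the data were seen.

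**Working it through.** **1. The plan's own figure.** Inputs from Sample size: reductions of 1.5 (SD 1.5) and 0.5 (SD 0.5) mg/l, alpha 5%, power 80%; sidedness is not stated and two-sided is assumed.

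- Difference = 1.5 - 0.5 = 1.0. Root-mean-square SD = √[(1.5² + 0.5²)/2] = √1.25 = 1.118. Standardised effect = 1/1.118 = 0.894.
- n per arm = 2 × (1.960 + 0.842)² × 1.25 / 1.0² = 19.6, so 20 (normal), or 21 with the t distribution.

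The stated 42 per arm is not reproduced; 21 per arm is 42 in total. That is a separate matter. What counts here is that the calculation is for one comparison at one 5% level and points to no visit.

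**2. Which contrasts the text allows.** GEE is an estimation method, not a contrast. With visits at 3, 6 and 12 months it can give:

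- one time-averaged group difference;
- one joint group-by-time test;
- three visit-specific differences.

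If baseline is modelled as a response, the group main effect is not the treatment effect at all. The article does not choose among these.

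**3. Error rate if any visit could be claimed.** This is a hypothetical success rule, not one the article states. For independent tests the risk is 1 - 0.95³ = 14.3%. For correlated tests it was simulated with three equicorrelated normal statistics (2,000,000 draws per correlation). The correlations are assumptions, because the article gives none.

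| Correlation between visit tests | Any of 3 visits | Any of 3 visits by either of 2 methods* |
|---|---|---|
| 0 | 14.3% | 18.1-21.6% |
| 0.5 | 12.6% | 15.9-19.0% |
| 0.7 | 10.9% | 13.9-16.6% |
| 0.8 | 9.8% | 12.4-14.9% |
| 0.9 | 8.4% | 10.7-12.8% |

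*Adjusted and unadjusted tests, correlation between methods 0.95 to 0.8.

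**4. A plausible point within that range.** Suppose CRP has equal correlation r between all occasions (compound symmetry). Two changes from the same baseline then have covariance r - r - r + 1 = 1 - r and variance 2(1 - r) each, in units of the outcome variance. Their correlation is (1 - r)/[2(1 - r)] = 0.5, whatever r is. The 0.5 row then applies, about 12-13%. A simulation of t tests on change scores with 42 per arm (6,000 null trials per setting, compound symmetry, r from 0.3 to 0.8) gave 12.3-13.6%, with a Monte Carlo standard error of about 0.4 percentage points.

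**5. Error rate with one fixed contrast.** It is nominally 5%. A joint three-visit Wald test with a chi-square reference ran at 5.9-6.9% in the 42-per-arm simulation, with adjusted regression standing in for GEE. A joint test would therefore want a small-sample reference distribution.

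**The case against.** The strongest case against is that the article is coherent as a summary: one primary variable, repeated measurements and a repeated-measures model. Which coefficient of that model is primary could be left to an analysis plan that is not shown. Sample size also speaks of the change in the singular, which argues against reading several separate primary tests into the plural elsewhere. This has some force, and it limits the point to a missing definition; it does not show that three tests are planned. It does not remove the point. The time point or summary belongs to the outcome's definition, the article has a dedicated section for that outcome, and the sample size rests on it.

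A reader might infer more: that the t tests and the GEE model have equal standing, that a positive result by either at any visit counts, and that the primary claim therefore carries a 12-19% false-positive risk. The text does not support this. GEE is the only method assigned to comparing changes between groups, and the section on confounding says that treatment effects on the primary and secondary outcomes are assessed with adjustment, which an unadjusted t test cannot provide. The t tests appear beside chi-square tests as univariate analyses and are not linked to CRP change. No success rule based on any visit or either method is stated.

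It is also fair to say that an average over visits is only one valid choice. One named visit would control the error equally well.

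**Conclusion.** The point holds as a definitional gap. No visit, summary or model term is fixed as the primary CRP contrast, and neither the sample size nor the naming of GEE closes the gap.

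The size is conditional. If any of the three visits could be claimed, the false-positive risk is about 8-14% (correlation between visit tests 0.9 to 0), or about 12-13% for change scores under compound symmetry. If unadjusted tests were interchangeable with adjusted ones as well, it would be about 16-19% at a visit correlation of 0.5 and about 11-13% at 0.9. With one fixed GEE contrast it is nominally 5%. These figures rest on assumed correlations and on a success rule that the article neither states nor excludes, so none of the inflated rates should be quoted as the error rate of this trial.

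**What to change.** Before unblinding, state one primary test in Primary outcome and repeat it in Statistical analyses. For example: the GEE test-versus-control difference in CRP averaged over 3, 6 and 12 months, adjusted for baseline CRP, at two-sided 5%. This suits the abstract's wording and the 12-month aim. One named visit would serve as well. Add baseline CRP to the covariate list and say which contrast the sample size refers to. Label the remaining visit-specific contrasts as secondary and the univariate t tests as descriptive.

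The cost is a few sentences and no new data or visits. Trial status says that a first block is already being treated, so the change should be recorded as a dated amendment. Randomization says that codes are kept until the analyses end, so the contrast can still be fixed blind. The downside is that a significant result at a single other visit no longer counts as primary success.

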### Secondary outcomes

Secondary outcomes will include:

•Non-invasive measurements of endothelial function (FMD);

•Traditional cardiovascular risk markers (total cholesterol, LDL-C, HDL-C and triglycerides);

•Proinflammatory biomarkers (IL-1β, IL-6, TNFα and fibrinogen);

•Endothelial function biomarkers (ICAM-1, VCAM-1 and E-selectin).

### Independent/exposure variables and confounding

The main exposure variable will be composed by test and control periodontal treatments. The impact of each treatment on the primary and secondary outcomes will be evaluated controlling for the following confounding factors: age, gender, BMI, physical activity, glycated hemoglobin, use of oral hypoglycemic drugs, smoking exposure and subgingival microbiota.

### Statistical analyses

Continuous variables will be described using means and standard deviations or median and range in case of asymmetric distribution of data. Categorical variables will be presented using frequency distribution. An intention-to-treat approach will be used in the analysis of this trial taking into consideration all dropouts during the follow-up period.

Univariate analyses will be conducted using chi-square and *t* tests for independent samples. Multivariate models will be fitted using generalized estimating equations to compare changes in each outcome according to test and control periodontal treatment groups controlling for confounding factors. *P* values <0.05 will be considered statistically significant. A statistical package (Stata 12 for Macintosh, STATA Corp., College Station, TX, USA) will be used. The individual will be considered the unit of analysis.

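### The models of change adjust for eight listed factors but not for the baseline value of the outcome, although baseline CRP is measured

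*Protocol article*

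**What the plan says.** The article's Primary outcome section reads: "The primary outcome of the present trial will be changes in serum concentrations of C-reactive protein". Under Statistical analyses, chi-square and t tests are listed as univariate analyses. The models are then described: "Multivariate models will be fitted using generalized estimating equations to compare changes in each outcome according to test and control periodontal treatment groups". They are to be adjusted for confounding factors. The section Independent/exposure variables and confounding names those factors for the primary and secondary outcomes: "age, gender, BMI, physical activity, glycated hemoglobin, use of oral hypoglycemic drugs, smoking exposure and subgingival microbiota". That is eight items, and the baseline level of the outcome is not one of them.

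The Blood markers section has CRP and the other markers measured at baseline and at 3, 6 and 12 months. Under Study protocol, flow-mediated dilation also has a baseline measurement. The missing covariate is therefore already collected for every outcome.

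Skewed data are mentioned once, for description only: "means and standard deviations or median and range in case of asymmetric distribution of data". The article gives no family, link or scale for the models, and neither plans nor excludes a transformation.

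**The concern.** A change score subtracts the whole baseline value, although the follow-up value usually tracks baseline only in part. Patients who start high tend to fall and patients who start low tend to rise, whatever the treatment. If one arm happens to start with higher CRP, part of its apparent fall is regression to the mean. Randomization is stratified only by the extent of periodontitis, so it does not balance baseline CRP directly, and none of the eight listed factors is a substitute for it.

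At stake are the precision of the CRP contrast and its protection against chance imbalance. The same holds for the lipids, cytokines, adhesion molecules and flow-mediated dilation, because one model form is used for each outcome.

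**Working it through.** **Inputs.** All come from the Sample size section. The planned effect is given as "reductions in C-reactive protein of 1.5 mg/l (standard deviation = 1.5) and 0.5 mg/l (standard deviation = 0.5) in the test and control groups, respectively". For the error rates the section says: "Alpha and beta errors of 5% and 20%, respectively, were used in the estimation". The stated size is: "It was estimated that 42 individuals in each treatment arm will be necessary". On dropout it says: "An attrition rate of 20% is expected during the study; consequently, 50 patients in each group will be included". I assume two-sided testing, since sidedness is not stated. The correlation rho between baseline and follow-up is not given, so I use 0.3 to 0.8.

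**1. The plan's own figure.** The difference is 1.5 − 0.5 = 1.0 mg/l. The pooled SD is √((1.5² + 0.5²)/2) = √1.25 = 1.118. Then n = 2 × (1.96 + 0.84)² × 1.25 / 1.0² ≈ 19.6, so 20 per arm (21 with the exact t distribution). The stated 42 per arm does not reproduce. It equals 2 × 21, but the article does not say how it arose. That is a separate matter; here it means only that the planned size is generous for these inputs.

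**2. Power without baseline adjustment.** Power = Φ(1.0 / (1.118 × √(2/n)) − 1.96).
- n = 42: Φ(4.10 − 1.96) = 98.4% (exact t 98.2%).
- n = 40, that is 50 × 0.8: Φ(4.00 − 1.96) = 97.9% (exact t 97.7%).

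**3. Effect of the covariate.** With variance σ² at both times, the change has variance 2σ²(1 − rho) and the baseline-adjusted outcome has σ²(1 − rho²). The ratio is (1 + rho)/2, a reduction of (1 − rho)/2. Power is recomputed with the SD multiplied by the square root of that ratio. The last column starts instead from a true power of 80%: Φ(2.80/√ratio − 1.96).

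| rho (assumed) | Variance ratio | Reduction | Power, 42 per arm | Power, 40 per arm | If 80% unadjusted |
|---|---|---|---|---|---|
| 0.3 | 0.65 | 35% | 99.9% | 99.9% | 94% |
| 0.5 | 0.75 | 25% | 99.7% | 99.6% | 90% |
| 0.7 | 0.85 | 15% | 99.4% | 99.1% | 86% |
| 0.8 | 0.90 | 10% | 99.1% | 98.8% | 84% |

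The gain is 0.7 to 1.5 points at 42 per arm and 0.9 to 1.9 points at 40.

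**4. Chance imbalance.** With equal variances the regression slope on baseline is rho, so a baseline difference D between arms shifts the expected difference in changes by (1 − rho) × D in size: 0.7D at rho 0.3, 0.5D at rho 0.5, 0.2D at rho 0.8.

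**5. Three follow-up visits.** If the model averages the 3-, 6- and 12-month values and all pairs of visits have correlation rho, the mean follow-up has variance v = (1 + 2rho)/3 in units of σ². The mean change then has v + 1 − 2rho and the adjusted mean v − rho². The ratios are 0.625, 0.70 and 0.775 for rho 0.5, 0.6 and 0.7. Repeated visits do not remove the benefit, because every change shares the same baseline value.

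**6. Log scale, for illustration only.** Simulated power with log-normal CRP, 42 per arm, one follow-up, rho 0.5 on the log scale, a 40% reduction in the test arm and none in control (2,000 trials per row):

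| Log-SD (assumed) | Raw change | Raw, baseline-adjusted | Log change | Log, baseline-adjusted |
|---|---|---|---|---|
| 0.4 | 99.8% | 100% | 100% | 100% |
| 0.6 | 83% | 98% | 97% | 99% |
| 0.8 | 53% | 79% | 83% | 91% |
| 1.0 | 30% | 51% | 63% | 75% |

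The result depends almost wholly on a log-SD that the document does not give.

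**The case against.** The strongest reply is that nothing here is invalid. Randomization makes the comparison of changes unbiased on average. In simulations of log-normal CRP the type I error was 4.0% to 4.7% for the raw-change t test and for the baseline-adjusted analyses alike. The article is also a condensed text, and an unseen analysis plan could add baseline terms. The first part stands: this is a question of efficiency. The second stands only for what the article leaves open. It does state its covariates, and baseline is not among them.

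Three stronger readings are tempting and are not supported.

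- *The plan discards much of its power.* On the Sample size inputs, power is about 98% without the covariate. The large differences in step 6 need far noisier CRP than was planned. For example, with a median of 2.5 mg/l, rho 0.6 and log-SD 0.7, 0.85 or 1.0, the control-arm SD of change would be about 2.4, 3.6 or 5.5 mg/l, which is 5 to 11 times the planned 0.5.
- *The primary comparison is a t test on untransformed changes.* The t tests are labelled univariate, the comparison of changes is assigned to generalized estimating equations, and neither is named primary. That the scale is untransformed is inferred from silence on link and scale, which an article may leave to the analysis plan.
- *SDs equal to the means in the Sample size section point to a log-normal variable.* Those are means and SDs of reductions, not of CRP levels, and say nothing about how spread grows with level.

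**Conclusion.** The point holds as a modest, specific improvement. The stated covariate list omits the baseline value of the outcome, and including it would lower the variance of the treatment contrast by about 10% to 35% and protect against chance baseline imbalance. This rests on equal variances at baseline and follow-up, a common correlation in both arms, and an assumed rho of 0.8 to 0.3. On the article's planning values the power gain is about 1 to 2 points. If true power were only 80%, it would be about 4 to 14 points. The lack of a stated log scale is not a defect of the article. It supports only an optional addition, because asymmetric data are foreseen but dealt with only descriptively.

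**What to change.** Add the baseline value of each outcome as a covariate in its model, with baseline CRP for the primary outcome. Change can stay the declared outcome and mg/l the unit: with baseline in a linear model, the treatment estimate is the same whether the response is the change or the follow-up value. The cost is one more coefficient per model; no new data or visits are needed. The Trial status section describes a first block under treatment with recruitment continuing, and the Randomization section keeps the codes until the analyses end, so the amendment can be fixed without knowledge of results by arm.

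Optionally, prespecify a log-scale, baseline-adjusted analysis of CRP and the other skewed biomarkers, at least as a sensitivity analysis. Its cost is real but small: the effect becomes a ratio of geometric means instead of a difference in mg/l, the unit of the sample-size calculation, and values below the assay limit need a rule set in advance.
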